**3. Description of the project**

**3.1. Rationale and objectives of the study**

**3.1.1. Rationale**

Uterine leiomyomata are common pelvic tumors occurring in up to 20% of women over 30 years of age, and represent one of the most frequent indications for operative procedures in women of reproductive age. (Buttram et al 1981) The growth of the fibroids seems to be dependent of ovarian steroids and receptors for both estrogen and progesterone have been identified in fibroids (Wilson et al 1980, Soules et al 1982).

That progesterone may play a role in leiomyomata growth is further supported by the finding of a higher mitotic count in leiomyomata obtained during the secretory phase than in the proliferative phase of the menstrual cycle. (Kawaguchi et al 1989)

The antiprogesteron mifepristone is a synthetic steroid hormone that binds with high affinity to the progesterone receptor thereby preventing the effect of progesterone. Administration of mifepristone has various effects on reproductive function, depending on the dose and stage of the menstrual cycle. When administered in the follicular phase of the cycle, mifepristone inhibits the process of follicular maturation and blocks ovulation.

Previous studies have shown positive effects after treatment with mifepristone when administered 25-50 mg daily for 3 months. All women became amenorrhoeic during treatment and the size of the fibroids decreased with approximately 50% (Kettel et al 1994). Studies using even higher doses of mifepristone for longer periods than 3 months have not revealed any significant risk of endometrial hyperplasia (Murphy et al 1995).

Ovarian steroids also have an effect on breast tissue. Concern has been raised about hormone replace treatment (HRT) with estrogen and progesterone. Various antiprogestins have been proposed as effective for inhibiting tissue growth in the breast. It would therefore be of importance to evaluate the effect of antiprogestins on the breast tissue.

Apoptosis (programmed cell-death) and cell proliferation seem to be closely linked according to experimental evidence. Many proteins that can induce cell death are also components of the cell cycle (Meikrantz et al 1995, Huang et al 1997). The balance between cell proliferation and cell death determines tumor growth in the endometrium as well as in the breast tissue. Specific markers for proliferation (Ki-67) and apoptosis (proteins from the Bcl-2- family) have been identified.

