**3.3. Design and methodology**

**3.3.1. General outline**

This is a pilot study to evaluate the effect of mifepristone on uterine fibroids. The study will include 40 women with uterine fibroids, recruited from the waiting list for hysterectomy. After inclusion women will be randomized to treatment with mifepristone or a placebo (i.e B-vitamin tablets). An ultrasound examination will be performed at start and repeated every 4th week. The total volume of the uterus will be measured as well as each fibroid, and also a Doppler examination of the blood vessels to the fibroids. An biopsy from the fibroid will be obtained at the same time. Endomtrial biopsies will be obtained prior to study start and at surgery for safety reasons and will undergo histological analyses.

Blood will be drawn for analyses of liver function and hemoglobin values as well as estradiol, progesterone, LH, FSH, SHBG, androstendione and DHEAS once a month. A 24 hour urine collection for cortisol levels will be performed and a measurement of body composition with bioelectrical impedance analysis (BIA). This will give information about body cell mass, fat-free mass and total body water. These tests will be repeated after the treatment period.

Women that have not had a mammography during the last 12 months will be offered to have one before the start of the study. A fine-needle-aspiration, from one breast will be performed before, and after the treatment period, for cytological analyses of apoptotic and proliferative factors i.e. Bcl-2, Ki-67 and receptors for estrogen and progesteron. Fine needle aspirations will be performed at the Dept of Cytology, KS in collaboration with [name].

The women will be given Mifegyne 200 mg tablets or B-vitamins and instructed to divide the tablets into 4 parts. One quarter of the vitamin or Mifegyne tablet (50 mg mifepristone), will be taken orally every other day for 3 months. A diary card will be handed out for self registration of bleeding (days and amount), pelvic pain and any side effects.

After the treatment period the woman will undergo surgery as planned. After the uterus has been removed it will be weighed and biopsies from the myomas will be taken for analysis of apoptotic and proliferative factors i.e. Bcl-2, Ki-67 and steroid receptors. Finally the uterus will be examined by a pathologist as part of the usual routine procedure.

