**3.3.2. Criteria for selection of subjects**

A total of 40 women will be recruited among women that are already on the waiting list for hysterectomy.

Inclusion criteria:

- Uterine fibroids requiring treatment
- Good general health
- Willing and able to participate after giving informed consent

Exclusion criteria

- Need for immediate surgery
- Concomitant hormonal treatment (HRT)
- History of malignant disorder of the breast
- Any contraindication for mifepristone

Criteria for retrospective exclusion

Subjects may be excluded from analysis if one of the following applies:

- Any violation of the study protocol
- Lack of essential data

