**3.3.3. Subject allocation**

The women who are willing to participate and fulfill the inclusion criteria will be randomized to treatment with Mifegyne or B-vitamin (control group). The treatment will be double blind. Only the nurse instructing patients on how to divide the tablets will be aware of treatment group. The women will obtain once monthly 6 tablets of 200 mg mifepristone or 6 tablets of B-vitamin of which one quarter of a tablet will be taken every other day.

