## Statistics

*Sample size calculation*Assuming a standard deviation of 10% in the percentage volume change, 18
 subjects per group will be required to detect a difference of at least 10%
 in the percentage volume change between the treated and the placebo groups
 with 90% power, using a one-sided 5% level test. Allowing for a 10%
 drop outs, 20 subjects per group, or a total of 40, will be recruited into
 the trial.

*Analysis*

 Myoma volume: Repeated measures analysis techniques will be used. For each group, the
 change at each time point will be compared with the baseline value and the
 percentage change with respect to baseline will be estimated. A repeated
 measures model with the baseline volume as a covariate will be used to
 compare the volume at different times between the two groups. Changes will
 be plotted on the absolute scale and will also be expressed as percentage
 change with respect to baseline.

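### The protocol plans no direct record of tablet intake, yet lets women be dropped from analysis for any protocol violation, so exclusions for missed doses would rest on chance knowledge

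*Protocol*

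**What the plan says.** Protocol section 3.3.1 describes the tablets: "The women will be given Mifegyne 200 mg tablets or B-vitamins and instructed to divide the tablets into 4 parts". One piece "will be taken orally every other day for 3 months". The same section lists what the diary is for: "A diary card will be handed out for self registration of bleeding (days and amount), pelvic pain and any side effects". Intake is not on that list.

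Section 3.3.3 covers supply: "The women will obtain once monthly 6 tablets of 200 mg mifepristone or 6 tablets of B-vitamin". It does not mention returning or counting unused pieces. It also says that only the nurse who teaches tablet division knows the allocation.

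The laboratory programme in section 3.3.1 includes "estradiol, progesterone, LH, FSH, SHBG, androstendione and DHEAS once a month", but no mifepristone level. The sections on laboratory analysis and statistics do not mention intake.

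Section 3.3.2 allows retrospective exclusion from analysis on two grounds, one of which is "Any violation of the study protocol".

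**The concern.** Missing doses is an obvious departure from the protocol, so the exclusion rule in section 3.3.2 reaches it. The rule has no systematic record behind it. A missed dose would come to light only if a woman mentioned it or someone asked. Such conversations need not be equally common in the two arms, because side effects and bleeding changes prompt them and an active drug may alter both. Exclusions made this way could remove different kinds of women from each arm, and the groups would then no longer be comparable by randomisation.

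A second cost falls on interpretation. This is a pilot of an alternate-day regimen, and its main product is the size of the volume effect. If the effect is weak, readers will ask how much drug was taken, and the planned data would answer only indirectly. An analysis plan cannot recover intake that was never collected, so this belongs in the protocol.

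**Working it through.** **Sample size, reproduced first.** Inputs from the Statistics section: SD 10 points, difference 10 points, one-sided 5%, 90% power, 10% drop-out.

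- n per arm = 2 × (1.645 + 1.282)² × (10/10)² = 17.1, rounded up to 18. This matches "Assuming a standard deviation of 10% in the percentage volume change, 18".
- With drop-out: 18 / 0.90 = 20 per arm, 40 in total. This also matches.
- Power at 18 per arm: standard error = 10 × √(2/18) = 3.33, and Φ(10/3.33 − 1.645) = Φ(1.355) = 91%. The exact t calculation gives 90%.

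**Doses.** Treatment days / 2: 84/2 = 42, 90/2 = 45, 92/2 = 46.

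**Pieces supplied against pieces scheduled.** Section 3.3.3 supplies 6 × 4 = 24 quarters a month, or 72 over 3 months. The alternate-day schedule uses about 15 a month, or 45. With perfect intake, 72 − 45 = 27 quarters are left over. The two statements must be reconciled before a count of returned pieces can be read as intake.

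**Exclusions.** One woman is 1/20 = 5% of an arm. The drop-out allowance is 20 − 18 = 2 women per arm, so a third loss or exclusion takes an arm below its planned 18. The size of any bias cannot be computed, because it depends on who is excluded and why.

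**Illustrative dilution.** The non-intake shares are assumptions; the Protocol gives none. All rows use a 10-point effect, SD 10, 18 per arm and one-sided 5%.

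| Assumed model | 10% | 20% | 30% |
|---|---|---|---|
| That share of treated women take nothing (simulated t-test, 40,000 trials) | 82% | 73% | 62% |
| Same, normal approximation | 84% | 75% | 64% |
| Effect falls in proportion to that share of doses missed (normal approximation) | 85% | 77% | 68% |

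- Proportional model, 20% missed: Φ(8/3.33 − 1.645) = Φ(0.755) = 77%.
- Take-nothing model, 20%: treated-arm SD = √(100 + 0.8 × 0.2 × 10²) = 10.77; standard error = √((100 + 116)/18) = 3.46; Φ(8/3.46 − 1.645) = 75%.

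**If the effect is near 50 points.** With 10, 20 or 30% taking nothing, the expected difference is 50 × 0.9 = 45, 50 × 0.8 = 40 or 50 × 0.7 = 35 points. Power stays above 99% in each case.

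**Dividing by the adherent share.** Suppose, as an assumption, that 70% adhere and gain 10 points while 30% take some pieces and gain 5. The difference is 0.7 × 10 + 0.3 × 5 = 8.5. Dividing gives 8.5 / 0.7 = 12.1, about 21% above the true 10. With 45 separate doses, partial intake is the likely pattern, so this correction should not be used.

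**The case against.** - **The diary sentence may be a summary.** The card itself is not shown, and section 3.3.8-10 sends all data to the patient file. A dose line might exist. This stands in part: the documents support saying that the Protocol provides for no direct record, not that none was kept.
- **Intake leaves traces.** A reader might infer that a weak or null result could not be told apart from tablets not taken. The documents do not support that. Section 3.1.1 says of earlier daily treatment: "All women became amenorrhoeic during treatment and the size of the fibroids decreased with approximately 50" per cent. It also says mifepristone given in the follicular phase blocks ovulation. Continued menses or ovulatory hormone values in a treated woman would therefore hint at gross non-intake. This stands, with limits. Neither measure is assigned to checking intake, and bleeding is itself an outcome (objective 4). The amenorrhoea came from daily dosing, so non-response and non-intake could look alike. Partial intake would not show, and nothing marks intake of the B-vitamin tablets.
- **The power loss is assumed.** The shares come from outside the Protocol and the answers depend on the model. Section 3.6 cites effective doses from 12.5 mg and a long half-life, so occasional missed pieces may dilute little. Some women who stop may already fall within the 10% drop-out allowance. All of this stands, and the figures are illustrations only.
- **More intake data could feed more exclusions.** This stands for as long as the section 3.3.2 rule remains, so both must change together.

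**Conclusion.** The point holds in a limited form. The Protocol plans no direct record of intake for about 45 self-quartered doses, while permitting exclusion for any violation. Followed as written, exclusions for missed doses would rest on chance knowledge and could bias the comparison between arms, by an amount the documents do not allow to be computed.

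Lost power is the lesser issue. Under assumed non-intake of 10 to 30% and a true effect of only 10 points, power falls to between 62 and 85%, depending on share and model. If the effect is near the 50% cited from daily dosing, power is not at risk and only the estimate shrinks. That smaller estimate is still a valid effect of assigning the regimen.

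This is not a fatal flaw. It is cheap to repair before the trial and cannot be repaired afterwards.

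**What to change.** 1. Add a diary line for the date of each piece taken.
2. Reconcile sections 3.3.1 and 3.3.3 on quarters supplied (24 a month) and scheduled (about 15). Then have returned pieces counted at each monthly hand-out by the nurse who already knows the allocation, so that nobody else is unblinded.
3. Report intake by arm.
4. Replace the section 3.3.2 exclusion for any violation with a main analysis of all randomised women with volume data, in the arm assigned. Any adherence-based analysis should be supportive only and should not divide by the adherent share.
5. Label any power figures for non-intake as illustrations under stated assumptions.

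The cost is one diary line and a few minutes at each existing monthly hand-out. Self-reported intake tends to be somewhat optimistic, which is why the count is worth having alongside it. The sample size does not change.

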**3.3.2. Criteria for selection of subjects**

A total of 40 women will be recruited among women that are already on the waiting list for hysterectomy.

Inclusion criteria:

- Uterine fibroids requiring treatment
- Good general health
- Willing and able to participate after giving informed consent

Exclusion criteria

- Need for immediate surgery
- Concomitant hormonal treatment (HRT)
- History of malignant disorder of the breast
- Any contraindication for mifepristone

Criteria for retrospective exclusion

Subjects may be excluded from analysis if one of the following applies:

- Any violation of the study protocol
- Lack of essential data

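### The protocol lets randomised women be dropped from the analysis afterwards, at discretion, for any violation or missing essential data, so the fibroid-volume comparison can be biased in either direction

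*Protocol*

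**What the plan says.** Section 3.3.2 of the protocol has a block on retrospective exclusion, separate from the entry criteria. It reads "Subjects may be excluded from analysis if one of the following applies" and lists two triggers: "Any violation of the study protocol" and "Lack of essential data". Violations are not graded, and essential data are not defined.

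The Statistics section says of myoma volume that "Repeated measures analysis techniques will be used", with baseline volume as a covariate. It names no analysis population, so nothing there overrides section 3.3.2. The sample size rests on the same outcome: "Assuming a standard deviation of 10% in the percentage volume change", "to detect a difference of at least 10" percentage points between groups, "with 90% power, using a one-sided 5% level test". This gives 18 per group. After a 10% drop-out allowance, "20 subjects per group, or a total of 40, will be recruited into" the trial.

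Section 3.3.3 describes the treatment as double blind, with only the nurse who explains the tablet division knowing the group.

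**The concern.** Randomisation protects the comparison only while women are counted in the arm to which they were allocated. A rule that removes them later, for reasons that may follow from treatment or outcome, gives up that protection. Three features of the wording matter:

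- The rule is permissive, so two women with the same deviation can be handled differently.
- Any violation qualifies, however small. Section 3.3.1 asks for self-divided tablets every other day for three months, four-weekly ultrasound, monthly blood tests, a urine collection, biopsies and a diary. Minor deviations are likely, so many women could become excludable.
- Some deviations may be related to treatment. Side effects or lack of relief could lead to missed doses, and section 2.5 itself anticipates difficulty with the timing of hysterectomy.

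With 20 women per arm, removing two to four is 10-20% of an arm. That is enough to move the error rate or the conclusion if the removals are not neutral.

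**Working it through.** **1. The plan's own figure.** Inputs from the Statistics section: SD 10, difference 10 (percentage points of volume change), one-sided alpha 0.05, power 0.90.

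n per group = 2 × (1.645 + 1.282)² × (10/10)² = 2 × 8.57 = 17.1, rounded up to 18. With 10% drop-out, 18 / 0.90 = 20. Both stated figures reproduce.

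**2. Power if exclusions leave fewer women.** One-sided two-sample t-test with noncentrality (10/10) × √(n/2):

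| n per group | noncentrality | power |
|---|---|---|
| 20 | 3.16 | 92.8% |
| 18 | 3.00 | 90.2% |
| 16 | 2.83 | 86.8% |
| 14 | 2.65 | 82.4% |

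The allowance covers 20 − 18 = 2 women per arm. The last two rows need four and six losses per arm from all causes. They assume that the losses are unrelated to outcome.

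**3. False-positive rate.** The protocol gives no number or pattern of violations, so every mechanism here is an assumption. Setting: no true effect, 20 per arm, SD 10, and a one-sided 5% pooled t-test for benefit of mifepristone on a single percentage change. The t-test stands in for the repeated-measures model. Under outcome-related selection, each woman has a violation score correlated 0.3, 0.5 or 0.7 with her outcome, and the two or four women with the highest scores are removed.

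| Assumed mechanism | One-sided error |
|---|---|
| No exclusions | 4.97% |
| Unrelated to outcome (2 per arm, or 4 from the treated arm) | 4.9-5.0% |
| Same outcome-related selection in both arms, 2 or 4 per arm | 5.0-6.3% |
| Poor outcomes dropped from mifepristone arm only, 2 of 20 | 7.0%, 8.8%, 11.0% |
| Poor outcomes dropped from mifepristone arm only, 4 of 20 | 8.9%, 12.7%, 17.9% |
| Good outcomes dropped from mifepristone arm, 2 or 4 | 1.3-3.5% |

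The two rows for poor outcomes in the mifepristone arm leave the control arm intact. Removing the same number of controls at random gives similar values: 6.8-11.6% for two and 8.5-16.6% for four.

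**4. Discretion alone.** If exclusions are random but the better of the full and reduced analyses is reported, the error is 6.3% with two removed per arm and 6.8% with four. This needs no selection by arm, only freedom to decide after seeing both results.

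**The case against.** The strongest objection concerns size. A reader might infer that the rule inflates the false-positive rate two- to three-fold. Such values can be produced: dropping outright the one or two worst outcomes of 20 treated women gives 9.7% or 15.4%, which is 1.9 or 3.1 times 5%. But this requires exclusions that are selective by both arm and outcome and that favour mifepristone. The documents supply no input for that. Neutral exclusion gives no inflation, and the opposite selection makes the test conservative. This part of the objection stands.

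Blinding is a real protection, since it makes arm-selective decisions harder. It is incomplete. Section 3.6 says the comparator is a B-vitamin tablet because matching placebo was not available, and section 3.1.1 reports that all women in earlier studies became amenorrhoeic on treatment, so the arm may be guessed. Blinding also does not stop women from deviating because of what the treatment does to them.

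Two other inferences are not supported:

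- A reader might see a contradiction between the missing-data trigger and the repeated-measures model, which could use incomplete series. Because essential is undefined, the trigger may mean only that baseline or all follow-up volumes are missing. A woman without a baseline could not enter a model with that covariate anyway.
- A reader might say that the 10% allowance leaves these exclusions out. The protocol does not define drop-outs, and the two groups probably overlap.

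Finally, who decides, and whether before unblinding, is often left to a SAP, which may exist. Silence on those points is not the fault here. The permissive rule is, because the protocol states it outright and a consistent SAP would inherit it. The pilot label in section 3.3.1 does not remove the concern, since the trial is sized for a formal test.

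**Conclusion.** The point holds as a defect in the wording of section 3.3.2. Randomised women may be removed at discretion for any violation or for undefined missing data, and no all-randomised analysis offsets this. Following the plan as written can bias the volume comparison in either direction.

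No single inflation factor can be attached to it. Over the mechanisms tabulated, the one-sided error runs from about 1% to about 18%, and it is near 5% when exclusion is neutral. The upper part needs selection against poor outcomes in the mifepristone arm only. These figures rest on 20 per arm, two to four exclusions, assumed correlations of 0.3-0.7 and a t-test stand-in. The power loss needs no selectivity, but it falls below the planned 90% only if fewer than 18 per group remain. Confidence is high in the wording defect and low in any particular size.

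**What to change.** Replace the retrospective exclusion block in section 3.3.2 with an analysis-set rule for the volume comparison:

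- The primary analysis keeps women in their randomised arm regardless of protocol violations and uses all available volume measurements in the repeated-measures model.
- The only women omitted are those without a baseline volume or without any follow-up volume. Their numbers and reasons are reported by arm. This is still a small departure from analysing everyone randomised and should be described as such.
- Any per-protocol set is a sensitivity analysis only, with violations classified before the code is broken.

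The change is to wording only and adds no visits, procedures or women. The one downside is that the estimated effect may be slightly smaller, because non-adherent women stay in.

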**3.3.3. Subject allocation**

The women who are willing to participate and fulfill the inclusion criteria will be randomized to treatment with Mifegyne or B-vitamin (control group). The treatment will be double blind. Only the nurse instructing patients on how to divide the tablets will be aware of treatment group. The women will obtain once monthly 6 tablets of 200 mg mifepristone or 6 tablets of B-vitamin of which one quarter of a tablet will be taken every other day.

